## Abstract

**Background:**

Patients undergoing major elective or urgent surgery are at high risk of death or significant morbidity. Measures to reduce this morbidity and mortality include pre-operative optimisation and use of higher levels of dependency care after surgery. We propose a pragmatic multi-centre randomised controlled trial of level of dependency and pre-operative fluid therapy in high-risk surgical patients undergoing major elective surgery.

**Methods/Design:**

A multi-centre randomised controlled trial with a 2 * 2 factorial design. The first randomisation is to pre-operative fluid therapy or standard regimen and the second randomisation is to routine intensive care versus high dependency care during the early post-operative period. We intend to recruit 204 patients undergoing major elective and urgent abdominal and thoraco-abdominal surgery who fulfil high-risk surgical criteria. The primary outcome for the comparison of level of care is cost-effectiveness at six months and for the comparison of fluid optimisation is the number of hospital days after surgery.

**Discussion:**

We believe that the results of this study will be invaluable in determining the future care and clinical resource utilisation for this group of patients and thus will have a major impact on clinical practice.

**Trial Registration:**

Trial registration number - ISRCTN32188676

## Background

Patients undergoing major elective or urgent surgery are at high risk of death or significant morbidity. Death around the time of surgery accounts for nearly one in 20 of all deaths in the UK and the rates are not significantly declining. Amongst the patients who survive, many suffer major complications with subsequent impairment of health and quality of life.

The National Confidential Enquiry into Peri-operative Deaths shows that such deaths are commonly associated with cardiac complications [1,2]. Putative contributory factors include a lack of High Dependency Unit (HDU) and Intensive Care Unit (ICU) beds, and suboptimal pre- and post-operative ward care. The Department of Health's report "Comprehensive Critical Care" [3] proposed that an HDU facility should care for frail patients who require monitoring or specialised analgesia after surgery without the immediate availability of medical staff, whereas an ICU-based HDU facility should care for patients requiring more detailed observation or intervention, including immediate availability of experienced medical staff. This simple system offers much to be commended as an attempt to allow more cost-effective and flexible utilisation of critical care services. However, there has been little research on the effects of ICU care alone on outcome from major surgery and these guidelines are based on expert opinion rather than empirical evidence. Further, they have not been routinely adopted and implemented into current clinical practice; only around 60% of hospitals have ward-based surgical HDU facilities and fewer hospitals have ICU-based HDU facilities [1,2]. "Comprehensive Critical Care" [4] also identified a need for a greater evidence-base to justify the huge clinical resources that are currently invested in critical care services throughout the UK. The question remains whether routine ICU-based postoperative care improves outcomes after major surgery in a cost-effective manner.

There is also evidence that peri-operative risk can be reduced by specific interventions applied before surgery. Pre-operative optimisation and supranormalisation aims to 'optimise' cardiac index and oxygen delivery through a pre-operative fluid and inotrope strategy that is maintained in the intra-operative and early post-operative periods [5-7]. Early randomised studies suggested a significant outcome advantage from this strategy. Wilson *et al *[6] found a mortality of 17% in the control group compared to 3% in the treatment group and claimed that this represented a cost-effective improvement in peri-operative care [6]. This study has, however, been criticised because of the poor outcome in the control group. Amongst those who consider pre-operative optimisation and supranormalisation to be effective, there is debate as to which aspect of the strategy brings about the reduction in mortality. Furthermore, the practicality of 'full' pre-operative optimisation and supranormalisation is limited because ICU-based care is required both before and after surgery. This has led to consideration of whether components that could be applied outside an ICU setting might still be useful.

This proposal is for a randomised controlled trial to test two of the most promising (but controversial) aspects of peri-operative care: firstly, a simple and practical approach to pre-operative preparation using ward-based intravenous fluid therapy; and secondly, the routine provision of intensive care facilities after surgery. We aimed to test whether ward-based pre-operative fluid loading and post-operative higher levels of dependency are effective and cost-effective in high-risk surgical patients undergoing major elective and urgent surgery.

## Methods/Design

A multi-centre, prospective, randomised, controlled trial with a partial 2 * 2 factorial design conducted in three UK hospitals, coordinated from the Centre for Healthcare Randomised Trials (CHaRT) in the Health Services Research Unit, University of Aberdeen [8,9]. The design features and estimates used in this protocol were further informed by the results of a 15-week pilot of the proposed protocol undertaken in Aberdeen Royal Infirmary, during which 23 patients were recruited.

### Research question

This trial aims to address the question whether: 1) ward-based pre-operative fluid optimisation and/or 2) routine post-operative ICU-based care for high risk surgical patients undergoing major elective and urgent surgery improves outcome and is cost-effective.

### Interventions to be evaluated

Patients will be randomised to a) pre-operative or standard regimen; and then secondly to b) ICU or HDU for post-operative care. The partial nature of the factorial design recognises that some patients may not be able to be randomised to the ICU or HDU comparison (as ICU beds cannot always be guaranteed).

### Pre-operative fluid therapy or standard regimen

In the pre-operative fluid therapy group patients will be electively commenced on pre-operative fluid therapy (25 ml/kg) using Hartmann's solution over six hours before surgery in the ward setting. In the standard fluid regimen no routine pre-operative fluid therapy will be given. All patients receiving bowel preparation will be given an additional 10 ml/kg Hartmann's solution in the 12 hours before surgery irrespective of trial group allocation (as this is deemed to be best clinical practice). Patients receiving "Klean-prep" bowel preparation with 4 litres of oral fluid will not receive additional IV fluids.

### ICU or HDU for post-operative care

The ICU care group will have initial post-operative care undertaken in the ICU under the care of ICU clinicians [3]. The HDU care group will have initial post-operative care undertaken in a surgical HDU under the care of the surgical team [3].

All non-protocol fluid prescriptions and other management decisions (including the movement of the patients through differing levels of dependency) will be made by the clinically responsible medical staff.

### Inclusion criteria

Inclusion criteria include patients undergoing major elective and urgent abdominal and thoraco-abdominal surgery who fulfil high-risk surgical criteria [10] who have signed informed consent. These high risk criteria include high risk type of surgery, presence of ischaemic heart disease, history of congestive heart failure, history of cerebrovascular disease, insulin therapy for diabetes and pre-operative serum creatinine > 2 mg/dl. Patients who undergo open, laparoscopic or laparoscopically-assisted surgery will be eligible.

### Exclusion criteria

Exclusion criteria will include New York Heart Association grade IV heart failure; clinician concern about safety of interventions; emergency surgery; chronic renal failure/creatinine > 300 umol.L^-1^, lack of informed consent; age < 16 years; pregnancy; major hepatic surgery, expected survival < 6 months.

### Study participants

Participants will be recruited from the elective operating schedules in the recruiting hospitals and informed consent obtained. Patients will, in general, be identified following a pre-assessment visit at a local hospital or following their initial appointment with the surgeon. They will be sent an information leaflet prior to their hospital admission, or given one at their appointment. Informed consent will be sought from these patients on their admission to hospital. Participants will be randomised through an interactive voice response (IVR) automated telephone randomisation service. A minimisation algorithm will be used, incorporating centre, age, sex and type of surgery [11]. All participants will be followed up daily for one week for major morbidity and mortality, then at hospital discharge and then one, three and six months after surgery for survival and quality of life.

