### Data analysis

The statistical analyses will be based on all people randomised who are retained in the study until the primary outcome time points, irrespective of subsequent compliance to treatment allocation. The principal comparisons will be a) all patients randomised to fluid optimisation versus all patients not allocated fluid optimisation and b) all patients randomised to routine ICU care versus all patients randomised to HDU for post-operative care.

Trial analysis will be undertaken using standard methods for two-group comparisons for continuous, binary and time-to-event outcomes [9]. All statistical analyses will be pre-specified in a Statistical Analysis Plan which will be agreed before any unblinded data is seen. Length of stay will be analysed using linear regression adjusted for the minimisation variables [11]. For the net benefit statistic, linear regression will also be used with adjustment for minimisation variables and the baseline EQ-5D score. Bootstrapping of the confidence interval for the mean difference in net-benefit will be performed and statistical significance determined on the basic of this interval including zero. Further details on the generation of the components of the net-benefit statistic are given in the economic analysis section. Health related quality of life measure will be analysed similarly. Mortality will be analysed using a Cox-proportional hazards model adjusted for minimisation factors. POMS will be analysed using logistic regression adjusted for minimisation covariates. A two-sided 5% significance level will be applied as evidence of statistical significance for the analyses. Corresponding confidence intervals will be presented.

For the fluid randomisation we plan to include patients recruited into the pilot study within the analysis as they have undergone the same interventions and have the same outcome measures collected (hospital length of stay). Pilot study data will not be used in the analysis of ICU length of stay as the primary outcome time point was changed from 1 year to 6 months as a result of the pilot.

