A single principal analysis is planned six months after the last person is recruited. If considered appropriate, follow-up of recruits will be extended at this time and a corresponding latter analysis will also be conducted once the latter follow-up data is available. Secondary subgroup analyses will be investigated through tests for interaction and will include patients with co-morbidities, cardiac risk [11], urgency and type of surgery. Stricter levels of statistical significance (2-sided 1% significance level) will be applied reflecting the exploratory nature of these subgroup analyses.

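### The covariates fixed for length of stay and net benefit omit the cardiac and co-morbidity criteria that define high risk, forgoing a modest gain in precision

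*Protocol article*

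**What the plan says.** Allocation (Protocol article, Study participants): "A minimisation algorithm will be used, incorporating centre, age, sex and type of surgery [11".

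Covariates (Data analysis) are named model by model:
- Length of stay, the primary outcome for the fluid comparison: "Length of stay will be analysed using linear regression adjusted for the minimisation variables".
- Net benefit, the primary outcome for the ICU/HDU comparison: "linear regression will also be used with adjustment for minimisation variables and the baseline EQ-5D score".
- Mortality: "Mortality will be analysed using a Cox-proportional hazards model adjusted for minimisation factors". The logistic model for POMS uses the same factors.

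Entry (Inclusion criteria): the high-risk criteria are listed as "high risk type of surgery, presence of ischaemic heart disease, history of congestive heart failure, history of cerebrovascular disease, insulin therapy for diabetes", followed by a raised pre-operative serum creatinine.

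Subgroups (Data analysis): the interaction tests "will include patients with co-morbidities, cardiac risk [11], urgency and type of surgery". They are labelled exploratory and held to a two-sided 1% level.

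The same section promises a Statistical Analysis Plan agreed before unblinded data are seen.

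**The concern.** The protocol treats its own risk factors unevenly. Type of surgery is an entry criterion, a subgroup factor, a minimisation factor and a covariate. The patient-level criteria (ischaemic heart disease, heart failure, cerebrovascular disease, insulin-treated diabetes, creatinine) help define who is high risk, and cardiac risk and co-morbidity are subgroup factors. Yet none of these items is a covariate in either primary model, and no reason is given. The Background also links peri-operative deaths to cardiac complications.

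The article names the covariates itself, so this concerns something it fixes and not a detail left for the analysis plan. Two things are at stake. The primary estimates may be less precise than the baseline data allow. And if the arms happen to differ in cardiac risk, the principal result will carry that difference, and any later adjustment would be post hoc and open to dispute.

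**Working it through.** **1. The lists side by side**

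| Item | Entry criterion | Planned subgroup | Minimised | Covariate, length of stay | Covariate, net benefit |
|---|---|---|---|---|---|
| Type of surgery | yes | yes | yes | yes | yes |
| Cardiac and co-morbidity items | yes | yes | no | no | no |
| Centre, age, sex | no | no | yes | yes | yes |
| Baseline EQ-5D | no | no | no | no | yes |

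**2. Reproducing the plan's figures** (Sample size; two-sided 5%, 1:1 allocation assumed, normal approximation)

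- ICU/HDU: n per arm = 2(1.96 + 0.842)²/0.45² = 77.5, so 78 per arm and 156 in total, as stated.
- Missing data: 156/0.90 = 173.3, so 174, as stated.
- Not reaching the second randomisation: 174/0.85 = 204.7, against 204 stated. The difference is rounding.
- Fluid comparison with 102 per arm: power is 81.5% at 0.4 SD and 94.6% at 0.5 SD, matching the claims of at least 80% and over 90%.

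None of these figures counts on any covariate gain.

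**3. Gain from adding cardiac risk**

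Let R² be the share of outcome variance that cardiac risk explains beyond the covariates already planned. The article does not give it, so a range is assumed. The residual SD is √(1 − R²), and

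power = Φ( d/√(1 − R²) × √(N/4) − 1.96 ).

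For example, with d = 0.45, N = 156 and R² = 0.10: 0.45/0.949 × 6.245 − 1.96 = 1.00, and Φ(1.00) = 84.2%.

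| Extra R² (assumed) | Net benefit, 0.45 SD, N = 156 | N for 80% power | Length of stay, 0.4 SD, N = 204 |
|---|---|---|---|
| 0 | 80.2% | 156 | 81.5% |
| 2% | 81.0% | 152 | 82.3% |
| 5% | 82.2% | 148 | 83.4% |
| 10% | 84.2% | 140 | 85.3% |
| 20% | 88.1% | 126 | 89.1% |

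**4. Chance imbalance in one risk factor**

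The prevalence p is not given either; 20% to 50% is assumed. Under a simple-randomisation approximation, the SD of the between-arm difference is √(2p(1 − p)/n).

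- 78 per arm: 95% range ±12.6 to ±15.7 percentage points; chance of a difference of 10 points or more, 12% to 21%.
- 102 per arm: 95% range ±11.0 to ±13.7 points; chance of 10 points or more, 7% to 15%.

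**5. What such an imbalance does to an unadjusted estimate**

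The 95% range of the shift is 1.96 × √R² × √(2/n). For R² of 2% to 10% this is ±0.04 to ±0.10 SD at 78 per arm and ±0.04 to ±0.09 SD at 102 per arm. For scale, the 95% confidence interval at 78 per arm has half-width 1.96 × √(2/78) = 0.31 SD, and that width already includes this source of variation.

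**The case against.** The plan is valid as written. Minimising on four factors and adjusting for them is coherent, and a subgroup factor need not be a minimisation factor or a covariate. A reader might infer that the primary comparisons are biased, or that the trial is underpowered. Neither follows. Omitting a prognostic factor does not bias a randomised comparison of means or inflate its type I error, and the stated sample sizes reproduce without any covariate gain.

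The size of the gain also rests wholly on assumed inputs. The Background ties cardiac complications to deaths, but the article does not say that these history items predict length of stay or net benefit. That step is inferred. Type of surgery, itself a high-risk criterion, is already in both models, and baseline EQ-5D may absorb part of the co-morbidity effect on net benefit. The article does not say how many criteria a patient must meet, so a complete record of every item at screening cannot be taken for granted.

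All of this stands, and it limits the point to efficiency and credibility. It does not remove the point. Baseline EQ-5D is not named for length of stay, and the subgroup tests need a baseline measure of cardiac risk in any case.

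**Conclusion.** The point holds as a modest improvement in efficiency; it is neither an error nor a contradiction. For an assumed extra R² of 2% to 10%, power rises by about 1 to 4 percentage points in each primary comparison. A gain near 8 points would need R² of about 20%, which nothing in the article supports. The benefit beyond power is that a chance difference in cardiac risk would be handled by a rule set in advance.

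Three stronger readings are tempting and are not supported:
- *The minimisation is faulty and must be changed.* Each added factor trades off balance on the others, and the Discussion says the trial is already being conducted. A covariate secures most of the benefit without touching allocation.
- *The Cox and POMS models also lose free precision.* In these models an added prognostic covariate changes the conditional estimand, because hazard and odds ratios are non-collapsible. It does not generally reduce the standard error, although it may raise power. Events may also be few. The earlier optimisation trial cited in the Background had mortality of 3% and 17% in its two arms; applied to 204 patients purely as an illustration, that is 0.03 × 204 ≈ 6 to 0.17 × 204 ≈ 35 deaths.
- *The cardiac-risk subgroup analysis is compromised.* An uneven split between arms does not bias an interaction test, and these tests are declared exploratory.

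**What to change.** Leave the minimisation factors as they are. In the Statistical Analysis Plan, before unblinded data are seen, add the baseline cardiac-risk measure required for the subgroup analyses as a covariate in the linear regressions for length of stay and for net benefit. Define its coding there, using the same definition for the covariate and the subgroup.

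For the Cox and POMS models, include it only if the number of events supports the extra parameters, and state that it changes the conditional effect being estimated.

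The cost is one or two extra parameters per model, with little or no gain if cardiac risk adds little beyond age, type of surgery and EQ-5D. Confirm that the measure is recorded for every randomised patient, including the pilot patients whom the Data analysis section plans to include in the fluid comparison.

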### Outcome measure

#### a) Pre-operative fluid therapy or standard regimen

The primary outcomes outcome is the number of hospital days after surgery (length of stay).

#### b) Routine ICU or HDU for post-operative care [3]

The primary outcome is cost-effectiveness at six months, measured by the Net Benefit statistic which is calculated using the following equation: ((λ * QALY) - costs) where λ indicates society's 'willingness to pay' (λ is typically set at £20,000 and this value will be used for the main analysis); QALYs are calculated using EQ-5D scores and costs include both primary and secondary care costs.

For both comparisons, secondary outcomes include measures of health status at one month after surgery measured using SF-36 by patient completed survey [12,13](with appropriate adjustment to accommodate for patients who die); changes in health status and quality of life over 6 months after surgery and quality of life at 48 hours, three and six months after surgery measured using SF-36 [12,13] and EQ-5D [14]; QALY calculated using EQ-5D. Other secondary measures include measures of health care costs including full hospital costs (driven by critical care utilisation and hospital length of stay) and primary care costs. Mortality will be measured using time-to-event analysis and the level of major morbidities in hospital using Post-Operative Morbidity Survey (POMS) [15]. The decision to discharge the patient from hospital was made by the caring team with no involvement of the study personnel. Study outcome measured during hospital stay were measured by study personnel not blinded to the intervention. Outcomes measured after hospital discharge were measured by study personnel blinded to the intervention.

### Sample size

As the smallest number of patients will be available for the comparison of ICU and HDU care (as not all patients will be able to be randomised to this comparison), this comparison drives the sample size calculation. We aim to be able to detect 0.45 standard deviations of a difference in the primary outcome (mean Net Benefit Statistic) between the two groups. For example, if the standard deviation of Net Benefits in both groups was about £10,000, this would equate to being able to detect a difference in the mean Net Benefit of £4,500. To be able to detect this level of difference with 80% power and a 5% level of significance, we will recruit 156 patients to this comparison. We further estimate that around 10% of patients will not have data available on all components of the cost-effectiveness at six months (which include data which is self-reported) and as such have inflated the number required to be recruited to this comparison to 174.

In the pilot study we found a 10% failure rate to progress from the first randomisation (pre-operative fluid) to the second randomisation (ICU versus HDU) because ICU care was not available. As such, the total sample size required to be recruited to the comparison of pre-operative fluid therapy or standard management needs to be at least 10% greater than that being sought for the ICU/HDU comparison. Conservatively, we have assumed that 15% will not be able to be randomised to the ICU/HDU randomisation and thus estimate that 204 patients be recruited to the study in total.

We have no reason to expect any loss to follow up for the primary outcome of the pre-operative fluid comparison (as the primary outcome is number of days in hospital after surgery). Ideally this comparison would have sufficient power to detect a 0.5 standard deviation change in number of days in hospital, with 80% power and 5% significance (requiring data on 128 patients to be available for analysis). In fact, a total sample size of 204 patients would allow a difference of 0.4 standard deviations of a difference to be detected with at least 80% power at a 5% level of significance (and over 90% power to detect a 0.5 standard deviation difference). The trial patient pathway is presented in figure 1.

